#### 2.1.5. Participant timeline.

The research team will review the elective surgical schedule at Maisonneuve-Rosemont Hospital to identify eligible patients at least one week before their surgery. After institutional consent is obtained, patients’ medical charts will be screened based on the study’s eligibility criteria. Potential participants will be contacted by telephone to explain the project and answer supplementary questions.

One their interest in the project is confirmed, candidates will meet with the research team on the day of their surgery to address any further queries, sign the consent form, and complete the standard preoperative questionnaire. Participants will undergo randomization following regional anesthesia and will receive surgery, with or without the VR headset, based on their allocation. A variety of preoperative, intraoperative and postoperative assessments relating to our outcomes of interest will be performed. Their involvement in the study will conclude upon discharge from the PACU. A detailed schedule of enrollment, interventions, and assessments is provided in Fig 2.

**Fig 2 pone.0327555.g002:**
[figure not shown]
Schedule of enrolment, interventions and assessments.

#### 2.1.6. Sample size.

The available literature on sedation requirements for adult patients using intraoperative VR headsets during surgeries under regional anesthesia is limited and heterogeneous, with studies reporting up to 93% reductions in sedation requirements [19], and others reporting no significant changes [20]. However, in a study evaluating lidocaine as an adjunct to reduce propofol requirements during pediatric colonoscopy, the lidocaine group consumed 35.5% less propofol than the control group, which was associated with significantly shorter awakening times, faster recovery times, and fewer involuntary movements during the procedure [21]. Similarly, a study comparing PCS to clinician-controlled sedation found a 39.3% reduction in propofol usage in the PCS group, which correlated with fewer episodes of deep sedation, fewer airway and breathing adverse events, and faster recovery times [22]. Therefore, for our sample size calculation, we estimated a 30% reduction of propofol usage in the VR group compared to the control group to be an approximate threshold for clinical significance. A two-sample t-test was used for the calculation, with a two-sided hypothesis test and a significance level of 0.05. To achieve 80% power, 90 participants were required, with the sample size inflated to 100 to account for attrition (e.g., dropout, protocol deviations).

Paravertebral block with propofol sedation has been validated as a safe and effective alternative to general anesthesia for breast cancer surgery, offering benefits such as higher turnover rates, reduced postoperative nausea, and faster hospital discharge [23]. According to historical data by Sessler et al., patients undergoing breast surgery with paravertebral block received a median propofol dose of 525 mg per patient [14].

#### 2.1.7. Recruitment.

Recruitment for this trial is anticipated to begin on October 30^th^, 2024. By screening all potential candidates and contacting them by telephone beforehand, we will ensure optimal participant enrolment. We expect to complete recruitment by September 2026. Experimentation and data collection will also occur throughout this period.

### 2.2. Assignment of interventions

Electronic randomization of the participants will be performed by an independent third party, using the National Cancer Institute’s Clinical Trial Randomization tool [24]. Specifically, we will randomize participants in a 1:1 ratio using a maximal randomization method, allowing a maximum tolerated imbalance of 3. The randomization sequence will then be implemented in the REDCap application (Vanderbilt University) [25]. Each participant’s allocation will be sealed in an opaque envelope and handed to the dedicated research staff not involved in patient care. The envelope will be opened at the patient’s entry into the operating ward, after confirming that the surgery will be performed under regional anesthesia. The intervention will not be blinded to participants or personnel after allocation.

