#### 2.1.3. Interventions.

Prior to entering the operating room, all participants will receive an explanation on the use of intraoperative PCS. For those in the intervention group, a short video will introduce all three VR scenarios, after which participants will select their preferred scenario, which will then be documented.

Upon arrival in the operating room, participants will undergo standard monitoring, including non-invasive blood pressure measurement, pulse-oximetry, and continuous electrocardiography using the Dräger Infinity C700 monitor (Dräger Medical, Lübeck, Germany). Throughout the entire duration of surgery, the NOL index finger probe, which is connected to the PMD-200 monitor (Medasense Biometrics Ltd, Ramat Gan, Israel) will be applied. All intraoperative data and events will be recorded on the research computer.

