The attending anesthesiologist will perform PV block before surgery according to their usual practice. Only anesthesiologists with a minimum of 10 PV blocks performed within the last year will be qualified to administer this procedure to trial participants. Standardized doses of intravenous (IV) sedation (0.15 mg/kg of propofol) and IV analgesia (0.5 mcg/kg of fentanyl) will be administered to all participants prior to realization of the PV block and will be repeated if necessary. Once the block is complete, the participant is positioned supine, and the surgeon is ready for disinfection, the VR headset will be applied to those in the intervention group and their chosen scenario will begin. A dedicated research staff member will be present in the operating room throughout the procedure to manage all aspects of the VR intervention, including assisting with headset application, adjusting the VR scenarios upon patient requests, and addressing any technical issues or patient discomfort related to the VR system. Notably, the interactive VR scenarios do not require significant hand or arm movement, as they rely solely on eye-tracking software to aim within the game. The only manual action required is pressing the controller trigger at specific time points. If at any time the patient expresses a desire to discontinue VR during the surgery, we will first offer them an alternate scenario. If they reiterate their willingness to stop, with or without having experienced the new scenario, the headset will be removed for the remainder of the surgery. In case of adverse events attributable to VR gear, such as cybersickness, discontinuation of VR immersion will be at the discretion of the anesthesiologist as well as the patient.

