Subgroup analysis will also be performed to explore how the selected initial VR scenario may impact our primary outcome. In the case of conversion to general anesthesia, the participant will be considered a protocol deviation. These participants’ data will still be included in the final analysis following an intention-to-treat (ITT) approach. Additionally, we will compare the prevalence of protocol deviations between the intervention and control groups to assess whether the conversion rate differs between conditions. To minimize protocol deviations, patient recruitment and randomization will only be finalized after the paravertebral block has been performed and its effectiveness has been confirmed by the lead clinician. If the block is deemed grossly ineffective, the patient will not be recruited or randomized.

As part of our exploratory analysis, we will investigate the relationship between the NOL index and propofol self-administration to determine whether NOL spikes serve as a predictor of subsequent propofol boluses. To achieve this, we will define a spike as any NOL score exceeding a threshold of 50 for a pre-specified duration of at least 10 seconds. We will then use time-series analysis to assess the temporal relationship between NOL spikes and propofol bolus administration. This will allow us to apply logistic regression and/or time-to-event analysis to determine whether NOL spikes significantly predict the likelihood of a propofol bolus within a predefined timeframe of up to 60 seconds.

All statistical analyses will be conducted using SAS, SPSS, or Python programming language with VS Code or Jupyter Notebook software.

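### The protocol times allocation in two conflicting ways: sections 2.1.3 and 2.2 imply that the arm is known before the paravertebral block, while sections 2.1.5 and 2.3.3 randomize only after it

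*Protocol article*

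**What the plan says.** Four sections of the protocol article bear on when the arm becomes known.

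- Section 2.2 (Assignment of interventions) opens the envelope at the patient's "entry into the operating ward, after confirming that the surgery will be performed under regional anesthesia". It also states that neither participants nor personnel are blinded once allocation is made.
- Section 2.1.3 (Interventions) begins before the operating room: "Prior to entering the operating room, all participants will receive an explanation on the use of intraoperative PCS". It continues: "For those in the intervention group, a short video will introduce all three VR scenarios, after which participants will select their preferred scenario". Next comes "Upon arrival in the operating room, participants will undergo standard monitoring", and after that "The attending anesthesiologist will perform PV block before surgery according to their usual practice". Propofol and fentanyl are given before the block and may be repeated. The headset goes on once the block is done and the patient is positioned.
- Section 2.1.5 (Participant timeline): "Participants will undergo randomization following regional anesthesia".
- Section 2.3.3 (Statistical methods) finalizes recruitment and randomization only once the block has been performed and the lead clinician has confirmed that it works. It adds: "If the block is deemed grossly ineffective, the patient will not be recruited or randomized". Participants converted to general anesthesia later stay in the analysis by intention to treat.

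**The concern.** Whether a block has failed is a matter of clinical judgement, and it decides who enters the trial. A block judged to have failed keeps the patient out altogether. A block judged adequate that later leads to general anesthesia leaves the patient in the intention-to-treat set. That sorting is harmless if it is made without knowledge of the arm. If the envelope is already open, the same judgement becomes a selection made after allocation, by staff who are not blinded.

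Two results would be exposed: the primary comparison of self-administered propofol, and the between-group comparison of conversions to general anesthesia that section 2.3.3 plans. Section 4.1.1 relies on patient-controlled sedation to limit the anesthesiologist's influence. That protection starts only when the patient controls the pump, so it does not cover a decision about entry made earlier.

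**Working it through.** The plan states no figure on this point that could be recomputed. The check is to set the sections side by side and ask whether one sequence satisfies all of them.

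**Order A, from sections 2.2 and 2.1.3**
1. Envelope opened on entry to the operating ward, once the plan for regional anesthesia is confirmed. The wording looks ahead to the surgery and mentions no block result.
2. Before the operating room, the intervention group alone sees the video and chooses a scenario. This step cannot take place unless the arm is known.
3. Arrival in the operating room and monitoring.
4. Pre-block propofol and fentanyl, then the block.
5. Positioning, then the headset.

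**Order B, from sections 2.1.5 and 2.3.3**
1. Consent and preoperative questionnaire on the day of surgery.
2. Block performed.
3. Block confirmed as effective by the lead clinician; patients with failed blocks are not randomized.
4. Randomization.
5. Surgery with or without the headset.

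**Can they be merged?**
- The sequence is generated in advance and sealed, so what matters is when the envelope is opened. Order A opens it at step 1. Order B makes the arm available only at step 4, after the block decision.
- Suppose the envelope is opened as in section 2.2 while entry is finalized as in section 2.3.3. The arm is then known before it is settled whether the patient is in the trial. A sealed opaque envelope conceals only until it is opened.
- Suppose instead that the block is done and confirmed somewhere outside the operating ward. Section 2.2 could then agree with sections 2.1.5 and 2.3.3. The text does not say this, and section 2.1.3 puts the block after arrival in the operating room and runs from it straight to positioning and the headset.
- Even in that case the video and scenario choice would follow intravenous propofol and fentanyl, because the arm would not be known earlier. The first scenario chosen defines the subgroup analysis in sections 2.3.3 and 4.1.3, so the time of that choice also needs to be fixed.

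The sections shown therefore give two orders, and following one departs from the other.

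**Size.** A figure for the bias would need the block-failure rate, the difference between arms in how often blocks are called failures, and the self-administered propofol use of such patients relative to others. The document gives none of these, so no figure is offered.

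**The case against.** The strongest reply is that no section says outright that the arm is revealed before the block. Section 2.1.3 says only that the block precedes surgery and names no room. The order is inferred from the narration and from the forward-looking wording in section 2.2. The schedule in Fig 2, which is not reproduced in the text available here, might settle it. This stands as a limit on certainty. It does not remove the conflict, because the arm-specific video before the operating room cannot be squared with randomization after a block that the same section narrates later.

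A reader might infer that the plan excludes allocated patients from the intention-to-treat set. It does not say so. The block-failure rule in section 2.3.3 is worded as applying before randomization and is sound when read alone. Exclusion after allocation is what could happen if staff follow the timing in section 2.2.

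A reader might also infer that early opening defeats the maximal randomization method. It does not. That method, with its tolerated imbalance of 3, limits how well future assignments can be guessed, and opening one patient's envelope early leaves this intact. The independent third party, the opaque envelopes and the use of research staff outside patient care protect allocation up to the moment of opening.

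Finally, a reader might assume that patients with failed blocks would use the most propofol, so that the bias has a known sign. The primary outcome counts self-administered doses only. Inadequate anesthesia is met with local anesthetic, fentanyl, ketamine and finally general anesthesia, and a patient converted early may self-administer little. Pre-block propofol is given by the clinician and is not part of the self-administered dose, so any effect of the arm being known at that stage is indirect.

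**Conclusion.** The concern holds as an inconsistency in the timing of allocation, with a real but unquantified risk of selection bias. Sections 2.1.3 and 2.2, as narrated, make the arm known before the block; sections 2.1.5 and 2.3.3 randomize after it. Under the first order, an unblinded clinician can know the arm when deciding whether the block has failed, and this could bias the primary comparison. Neither the size nor the direction can be derived from the document.

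The conclusion rests on two readings: that section 2.1.3 describes events in the order in which they occur, and that no unseen part of the plan places a confirmed block before entry to the operating ward. It does not claim that any patient has been or will be excluded after allocation. The correction is worth making because it costs almost nothing and closes the route to such selection.

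**What to change.** Bring sections 2.1.3 and 2.2 into line with sections 2.1.5 and 2.3.3:

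1. State that the envelope is opened, or the REDCap allocation revealed, only after block effectiveness has been documented. Record the time of both.
2. Move the scenario choice to fit. Either place the video and choice after the reveal and before the headset, or show the video to all consented participants and record a preference before any sedation. The first option means choosing after the pre-block drugs. The second avoids that but shows control participants a VR experience that they will not receive, in an open-label trial with a patient-driven outcome and a satisfaction rating. Either is workable if stated.
3. Keep in the intention-to-treat set and the flow diagram any participant whose allocation was opened before the block decision. Section 2.1.7 expected recruitment to start in October 2024, so such participants may already exist.

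The cost is a wording amendment, submitted to the ethics committee and updated in the registry as section 3.2 requires, plus one recorded time per patient. If the second option is chosen, control participants also spend a short time on the video. No additional patients are needed.

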### 1.3. Trial design

This is the protocol for an open-label, single-center randomized controlled trial.

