#### 2.1.4. Outcomes.

The primary outcome is the time-adjusted and weight-adjusted average or median self-administered dose of propofol in mcg/kg/min.

Secondary outcomes include

Initial enthusiasm at the idea of using a VR headset during surgery assessed by research staff on a 10-point Likert scale for all participants, prior to intervention allocation as part of a questionnaire;Level of anxiety and information requirement measured preoperatively by research staff using the Amsterdam Preoperative Anxiety and Information Scale (APAIS) [18];Incidence of intraoperative and postoperative adverse events such as bradycardia (heart rate < 50 bpm), desaturation (SpO_2_ < 92%) and hypotension (MAP < 60) as well as subjective adverse events, such as cybersickness or nausea documented intraoperatively by the anesthesiologist and research staff based on real-time clinical observation or patient self-reporting;Average or median total time, in minutes, during which the VR headset was worn, as well as the percentage of that time relative to the overall duration of the surgery, recorded by dedicated research staff in the operating room using a time log;Average or median total duration in minutes spent by the patient on the VR scenario chosen, and the order in which VR scenarios were presented, recorded by dedicated research staff in the operating room using a time log and a case report form (CRF);Percentage of patients that switched scenarios;Percentage of patients that removed the headset before the end of the surgery;Percentage of patients requiring additional local anesthesia;Weight-adjusted average or median administration of intraoperative IV fentanyl in mcg/kg;Weight-adjusted average or median administration of intraoperative IV ketamine in mg/kg;PACU length of stay (LOS) measured from PACU admission to PACU discharge, based on the PACU nursing records;Ease of use of the technology and enjoyment of the first scenario chosen assessed post-operatively on a 10-point Likert scale in the intervention group only as part of a postoperative questionnaire administered by dedicated research staff;Overall satisfaction with the experience assessed post-operatively on a 10-point Likert scale in both groups as part of a postoperative questionnaire administered by dedicated research staff.Exploratory outcomesNOL index readings over time per patient, recorded continuously intraoperatively via a finger probe, automatically stored and extractable by dedicated research staff from the PMD-200 monitor with precise timepoints. NOL index spikes will be defined;PCS bolus administration timepoints, automatically recorded by the pump device and extracted by dedicated research staff.

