### 2.3. Data collection, management and analysis

#### 2.3.1. Data collection methods.

We will collect data at baseline, intraoperatively and postoperatively to assess primary and secondary outcomes. Participant socio-demographic information, medical history and current medication, will be collected from their medical chart. Their education level and familiarity with VR technology will also be recorded through a preoperative questionnaire. Pre-operative anxiety levels will be assessed using the APAIS, a six-item questionnaire designed to measure both anxiety and the desire for information before surgery. The scale provides an overall anxiety score ranging from 4 to 20 and an information-seeking score ranging from 2 to 10, with higher scores indicating greater preoperative anxiety and a stronger desire for information, respectively. A postoperative questionnaire will be used to collect data on patient satisfaction. It is of note that, aside from the APAIS, both our preoperative and postoperative questionnaires are self-composed and have not yet undergone formal scientific validation.

NOL index data from the PMD-200 medical monitor will be automatically collected by the device. Other intraoperative events, such as propofol self-administration, as well as the use of fentanyl or ketamine, will be manually recorded. Postoperative outcomes will be collected through questionnaires administered to participants prior to their discharge from the PACU, at which point we will also record PACU length of stay (LOS). Adverse events of any kind will be documented when spontaneously reported or observed clinically.

We will monitor and document the number of participants who withdraw from the study. If a participant wishes to discontinue their involvement, they will be removed from the study at their request, and no further data will be collected or retained after their withdrawal.

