### 4.1. Limitations of study design

#### 4.1.1. Unblinded personnel.

Due to the nature of VR interventions, it is difficult for the patient, the anesthesiologist or the surgeon to be blinded to group allocation. We recognize that a sham intervention, such as having a patient wear a non-functional VR headset, could theoretically be considered to achieve blinding. However, we believe this approach presents several important limitations.

Firstly, a non-functional VR headset could potentially induce additional anxiety or feelings of claustrophobia, as it would restrict the participant’s vision without providing the immersive, open 3D environment intended to reduce anxiety; This unintended discomfort could, in turn, bias the results of our trial by exaggerating the perceived benefit of the active VR intervention. Secondly, while a sham headset might initially mask group allocation from personnel, it would not effectively blind participants, who would likely realize they are not receiving an active VR experience. This creates a significant risk that participants could inadvertently reveal their allocation during the procedure, which would hamper the effects of the blinding. Lastly, our trial is designed to compare a VR intervention to the current standard of care; a sham headset does not represent standard practice and would therefore lack clinical relevance in this context.

While our trial will not utilize blinding, the use of PCS minimizes the anesthesiologist’s influence on propofol administration, reducing performance bias.

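### Blinding is waived for all personnel, but the reasons given do not reach PACU staff, and a questionnaire with VR-only items falls inside the PACU length-of-stay interval

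*Protocol article*

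**What the plan says.** Section 1.3 gives the design: "This is the protocol for an open-label, single-center randomized controlled trial". Section 2.2 makes the waiver general: "The intervention will not be blinded to participants or personnel after allocation". No group of staff is excepted.

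Section 4.1.1 gives the reason, that "it is difficult for the patient, the anesthesiologist or the surgeon to be blinded to group allocation", and then explains why a sham headset was rejected. It offers one mitigation: "While our trial will not utilize blinding, the use of PCS minimizes the anesthesiologist’s influence on propofol administration, reducing performance bias".

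Section 2.1.4 defines the outcome at issue as "PACU length of stay (LOS) measured from PACU admission to PACU discharge, based on the PACU nursing records". The abstract names it as one of three secondary outcomes.

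On the questionnaire, section 2.3.1 says: "Postoperative outcomes will be collected through questionnaires administered to participants prior to their discharge from the PACU". According to section 2.1.4, ease of use and enjoyment of the first scenario are asked "in the intervention group only as part of a postoperative questionnaire administered by dedicated research staff", while the satisfaction item is common to the arms: "Overall satisfaction with the experience assessed post-operatively on a 10-point Likert scale in both groups".

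**The concern.** The waiver is wider than the argument for it. The reasons given concern people who are present while the headset is worn. Section 2.1.3 describes VR only in the operating room, so a PACU staff member would normally learn the arm only by being told. The one mitigation, patient-controlled sedation (PCS), protects the propofol outcome and does nothing for PACU LOS.

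LOS ends at an event that depends partly on what staff do. If those involved in discharge know that a patient had VR and expect a quicker recovery, the patient may leave sooner for that reason alone. The questionnaire bears on this in two ways. VR questions asked at the bedside can disclose the arm before discharge, and the additional items take up time within the interval in one arm only.

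What is at stake is the interpretation of a difference in LOS. Sections 1.1 and 2.1.6 link lower sedative use to faster recovery, so readers will look to LOS for support. An LOS difference should reflect recovery and not handling.

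**Working it through.** The plan states no figure on this point, so there is nothing to reproduce. The check compares the sections and then illustrates the scale.

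**Comparing the sections**

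1. Who is unblinded: all personnel (2.2).
2. Whom the reasons cover: patient, anesthesiologist, surgeon (4.1.1). PACU staff are not mentioned.
3. Where VR is used: in the operating room (2.1.3). No PACU use is described.
4. When LOS runs: PACU admission to PACU discharge (2.1.4).
5. When the questionnaire is given: before PACU discharge (2.3.1), so inside the interval in step 4.
6. How the questionnaire differs by arm: satisfaction in both arms; ease of use and scenario enjoyment in the VR arm only. Research staff administer it (2.1.4).

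Steps 1 to 3 show that the waiver extends beyond its justification. Steps 4 to 6 show a route by which the arm can be disclosed, and some time added, before LOS ends.

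**Scale, under assumptions**

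From the article: 100 participants randomized 1:1, hence 50 per arm, and a 0.05 significance level (2.1.6, 2.2, 2.3.3). Assumed, because the article gives neither: an LOS SD of 30 to 60 min and the size of any artefactual difference b. There is no true effect, and a two-sided two-sample t-test is used.

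The standard error of the difference is SD × √(2/50) = 0.2 × SD, which is 6 min at SD 30 and 12 min at SD 60. The rejection rate is the power of the t-test at a standardized difference of b/SD.

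| b (min) | b/SD at SD 30 | Rejection rate | b/SD at SD 60 | Rejection rate |
|---|---|---|---|---|
| 1 | 0.033 | 5.3% | 0.017 | 5.1% |
| 2 | 0.067 | 6.3% | 0.033 | 5.3% |
| 5 | 0.167 | 13.1% | 0.083 | 7.0% |
| 10 | 0.333 | 37.9% | 0.167 | 13.1% |

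The first two rows are a plausible range for a few extra rating-scale items. The last two would need a real change in discharge behaviour, and nothing in the article indicates whether one would occur.

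**Direction**

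Extra items lengthen the VR stay. Staff expectation in favour of VR would shorten it. The two act in opposite directions, so the sign of the net effect cannot be determined.

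**The case against.** The strongest reply is that the article is consistent. It declares the trial open-label, repeats this in the allocation section, and lists the absence of blinding as a limitation. PACU handover and discharge procedures are details that an article commonly leaves to the full protocol. This stands: there is no contradiction, and the absence of discharge criteria from the article is not counted as a fault. The point is a narrower one, that the stated waiver goes further than its stated reasons.

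A reader might infer that PACU nurses determine LOS. The article does not say so. It names nursing records as the data source, not who decides discharge or by what criteria. If fixed criteria or an anesthesiologist's order govern discharge, nurses' knowledge of the arm matters less. The argument needs only that staff behaviour can influence the recorded time.

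A reader might also infer that only VR patients are questioned, or that the questionnaire necessarily delays their discharge. Both arms receive one, the stated difference is a small set of items, and no time is added if it is completed before the patient is otherwise ready to leave.

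Two further objections stand in part. Staff caring for a nauseated patient might have reason to know about VR exposure, since section 4 names cybersickness as the most common anticipated side effect; the arm must therefore not be withheld where it is clinically needed. In addition, a readiness time is itself a staff judgement and does not measure the whole monitoring period named in section 1.2. It can supplement the stated LOS but should not replace it.

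**Conclusion.** The point holds in limited form. Blinding is given up for PACU staff without a stated reason, and a questionnaire with VR-only items is placed inside the interval that defines a secondary outcome.

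The added question time is probably negligible: at an assumed 1 to 2 min and an SD of 30 to 60 min, the rejection rate stays between 5.1% and 6.3%. Influence on discharge behaviour could matter more. The 7–13% (5 min) and 13–38% (10 min) figures show only what such shifts would do if they occurred. It would be wrong to read them as the trial's expected false-positive rate, because the article supports neither the SD nor the shifts.

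The primary outcome, self-administered propofol, is not affected. This is a low-cost improvement to one secondary outcome and does not threaten the trial's main conclusion.

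**What to change.** 1. In section 2.2, replace the general waiver with a statement that participants and operating-room staff are unblinded, and that PACU staff are not routinely told the allocation unless it is clinically needed.
2. Have research staff give the postoperative questionnaire only after the patient has been recorded as ready for discharge under the unit's existing practice, and before the patient leaves the PACU, where section 2.1.5 ends participation.
3. Report time from PACU admission to recorded readiness alongside the stated admission-to-discharge LOS. The questionnaire then lies outside the first interval, although it can still add to the second.
4. In section 4.1.1, acknowledge that blinding for LOS is partial.

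The cost is some protocol wording, a handover instruction and one additional time stamp, with no extra staff. Some patients will reveal their arm, and the questionnaire may keep a patient a few minutes after readiness. For patients already discharged, neither the concealment nor a readiness time that was not recorded can be recovered, so the change is worth most if made early.
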